##### Maternal blood concentration of O_2_•^−^

Maternal blood will be obtained at 12 weeks and 24-28 weeks in a heparin tube (BD vacutainer) and transported on ice. After 15 min, 30 μl of spin trap CMH (1-hydroxy-3-methoxycarbonyl-2,2,5,5-tetramethylpyrrolidine) will be added to 30 μl blood. The whole will be incubated on ice and transferred into a capillary after 5 min. The sample will then be snap frozen and stored in − 80 °C until analysis [34].

##### Immuno-histochemical staining for eNOS and iNOS

Placental tissue will be obtained shortly after delivery and stained for eNOS and iNOS as previously described by Du et al. [36]

### Statistical methods

#### Sample size calculations

As sample size determining factor, we took the RHI since this is an important variable in our study, there is normal distribution and the population standard deviation is known.

##### Prospective longitudinal study

For the physiologic study of the RHI in pregnancy we calculate that for a 95% confidence interval, a population standard deviation of 0.5 (as described in other populations for RHI) and a tolerable standard error of the mean (SEM) value of 0.1, 97 women have to be followed [37]. Taking at least a 10% dropout into account the starting sample size will be 110 women.

##### Matched case-control study

In a pilot study by Yinon [38] the RHI in normotensive pregnancies was 1.8, and in PE 1.5; in most populations standard deviation is 0.5 [37]. For 80% power and a two sided α = 0.05 and considering a 0.3 difference clinically relevant, the sample size for each group would be 44 *(**http://www.stat.ubc.ca/~rollin/stats/ssize/n2.html**);* which we consider the sample size for our cross-sectional study comparing pre-eclamptic patients with normotensive controls. The sample size of this study will be 90 patients, 45 in each group.

#### Descriptive statistics and data analysis

##### Prospective longitudinal study

For the physiologic study of the RHI in pregnancy we will calculate the reference values and 95% confidence interval. Longitudinal data will be plotted and a linear mixed-effects model with random intercept will be fitted. Percentiles for RHI, FMD and PWV/PWA will be calculated based on this model. Correlation coefficients between baseline RHI, FMD PWV/PWA, UA Doppler PI, fetal biometry, NLR, MPV, MAP, birth-weight percentile, eNOS, •NO and O_2_•^−^ will be analysed.

##### Matched case-control study

RHI, FMD, PWV/PWA, UA Doppler PI, fetal biometry, NLR, MPV, MAP, birth-weight, eNOS, •NO and O_2_•^−^ concentration and other continuous variables in PE versus healthy pregnancies will be tested for normality using the Shapiro Wilk Test. If there is normality, they will be expressed as mean, standard deviations and 95% confidence intervals and compared using two sided T test. If not, they will be expressed as median and interquartile ranges and compared using Mann Whitney U Test.

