##### Multicentre matched case-control study

The second part is a case control study where patients with pregnancies complicated by PE will be compared to normotensive controls, matched for maternal and gestational age, parity, smoking behaviour, BMI and ethnic group. Patients will be followed throughout (the rest of their) pregnancy and until 6 months postpartum. Matching will reduce the risk of bias.

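### The matched case-control arm is compared with tests for independent samples, which are conservative and give up precision if matched women are positively correlated

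*Protocol article*

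**What the plan says.** The Study design section of the protocol article, under the multicentre matched case-control study, says that women with pre-eclampsia (PE) are compared with normotensive controls "matched for maternal and gestational age, parity, smoking behaviour, BMI and ethnic group". It gives the purpose as "Matching will reduce the risk of bias". It does not say whether each case has her own control or whether the two groups are balanced as wholes.

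Under Sample size calculations, this arm is sized on RHI. The inputs are that "the RHI in normotensive pregnancies was 1.8, and in PE 1.5", a standard deviation of 0.5, 80% power and two-sided 5% significance. The result is 44 per group, with 45 per group (90 women) planned.

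Under Descriptive statistics and data analysis, the outcomes of this arm "will be tested for normality using the Shapiro Wilk Test". The rule that follows is: "If there is normality, they will be expressed as mean, standard deviations and 95% confidence intervals and compared using two sided T test". Otherwise they are "expressed as median and interquartile ranges and compared using Mann Whitney U Test". No paired test, pair effect or adjustment for the matching factors is named. The longitudinal arm, by contrast, is given a mixed-effects model with a random intercept.

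**The concern.** An analysis should follow its design. When controls are chosen to resemble cases on factors related to the outcome, matched women tend to be alike on that outcome. A test for independent samples leaves the shared variation in the error term, so the interval for the case-control difference is wider than the data warrant and the p-value is too large.

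The article itself gives reason to expect such likeness. Its Discussion describes flow-mediated dilatation rising until about week 32 and then levelling off or falling, and augmentation index falling in mid-pregnancy and rising late. Its Background reports nitric oxide increasing with gestational age. Gestational age is one of the matching factors.

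The same tests serve the primary objective, the comparison of oxidative-stress measures between normal and PE pregnancies. The arm is sized on RHI alone, so the 80% power statement does not cover those measures, and precision lost there is not known to be spare.

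A related weakness is that a Shapiro-Wilk result decides, outcome by outcome across about twelve named measures, whether means or medians are reported and which test is used. The effect measure is therefore not fixed before the data are seen.

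**Working it through.** **1. Which t test is meant?** The article does not label it. Three features point to the unpaired form:
- Its non-parametric partner is Mann-Whitney U, not the signed-rank test.
- Normality is checked on the variables themselves, not on within-pair differences.
- The sample size comes from an independent-groups formula (step 2).

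**2. Reproducing the plan's figure.** Inputs from Sample size calculations: difference 0.3, SD 0.5, two-sided alpha 0.05, power 80%.

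n per group = 2 × (1.960 + 0.842)² × 0.5² / 0.3² = 2 × 7.85 × 0.25 / 0.09 = 43.6, so 44.

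This is the stated figure, and it contains no within-pair correlation. The exact two-sample t version needs 44.6, so 45. At 45 per group its power is 80.4%.

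**3. Effect of ignoring pairs.** The article gives no rho, so a range is assumed. With 45 pairs:
- SD of a within-pair difference = 0.5 × sqrt(2(1-rho)). For rho = 0.3 this is 0.592.
- Ratio of unpaired to correct standard error = 1/sqrt(1-rho).
- Large-sample type I error of the unpaired test = 2 × [1 - Φ(1.96/sqrt(1-rho))]. This gives 3.9%, 1.9% and 0.6% at rho = 0.1, 0.3 and 0.5.
- Expected 95% half-width, unpaired = 1.987 × 0.5 × sqrt(2/45) = 0.209.
- Expected 95% half-width, paired, at rho = 0.3 = 2.015 × 0.592/sqrt(45) = 0.178.

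Type I error and power in the table come from simulation (20,000 data sets of 45 pairs, normal outcomes, true difference 0 or 0.3):

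| rho | SE ratio | Type I error, unpaired t | Type I error, Mann-Whitney | Power, unpaired t | Power, Mann-Whitney | Power, paired t | Half-width, unpaired / paired |
|---|---|---|---|---|---|---|---|
| 0 | 1.00 | 5.1% | 4.8% | 80.6% | 78.3% | 79.6% | 0.209 / 0.212 |
| 0.1 | 1.05 | 4.0% | 4.1% | 81.8% | 79.4% | 83.9% | 0.209 / 0.202 |
| 0.3 | 1.20 | 1.9% | 2.1% | 84.4% | 82.2% | 91.4% | 0.209 / 0.178 |
| 0.5 | 1.41 | 0.7% | 0.7% | 88.2% | 85.8% | 97.5% | 0.209 / 0.150 |

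The half-width ratio is slightly below the SE ratio (at rho = 0.3, 0.209/0.178 = 1.17) because the paired test has 44 degrees of freedom against 88.

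**4. Power given up by the unpaired t test.** At rho = 0.1, 83.9 - 81.8 = 2.1 points. At 0.3, 91.4 - 84.4 = 7.0. At 0.5, 97.5 - 88.2 = 9.3.

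**5. Is 45 pairs enough for a paired t test?** Pairs needed for 80% power are 46 at rho = 0, 42 at 0.1, 33 at 0.3 and 24 at 0.5. By formula, 45 pairs give 79.5% at rho = 0 and 83.5% at rho = 0.1.

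**The case against.** The strongest reply is that the article never says matching is individual. It speaks of two groups of 45 and gives no pairing rule. Under frequency matching there are no pairs, and a paired test could not be run. That stands. Pairing is a plausible inference from equal groups and six factors, but no more, so the fix needs a branch for each case. Even under frequency matching, the named tests make no adjustment for the matching factors.

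A second reply is that the stated aim of matching is less bias, not more precision, and that balance from control selection also benefits an unpaired comparison of means. This is also true. The point estimate is not in question; its interval and p-value are.

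A third reply is that the harm is modest. At rho = 0 nothing is lost, and the paired test is marginally weaker. This limits the size of the point but does not remove it, since the article's own account of change with gestational age makes a positive correlation likely.

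A reader might add that centre is absent from the analysis of a multicentre arm. A condensed article may leave that to the full protocol, so it is not part of this point. A reader might also want RHI analysed on a log scale. The article calls RHI normally distributed and sizes the arm on an absolute difference of 0.3, so it gives no support for that.

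**Conclusion.** The point holds as a mismatch between the stated design and the stated tests. This is a named method that does not fit, not detail left to another document. If matching is individual and the within-pair correlation is positive, intervals are too wide and tests conservative. Over an assumed rho of 0.1 to 0.5, the cost is about 2 to 9 points of t test power for the RHI target.

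Two stronger readings are not supported. A reader might infer that false positives are inflated, but with positive correlation the type I error falls below 5%. It would exceed 5% only with negative correlation (about 6.0% at rho = -0.1), which matching does not normally produce. A reader might also infer that the arm is underpowered as planned. The unpaired t test keeps at least 80% power for RHI at any rho of 0 or more; Mann-Whitney runs from about 78% to 86%.

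The sizes rest on assumed correlations, normal outcomes, 45 complete pairs and the article's SD of 0.5. For the oxidative-stress measures the article gives no effect size or SD, so only the relative loss (the SE ratio) carries over.

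**What to change.** In the matched case-control part of Descriptive statistics and data analysis, first state whether matching is individual or by frequency.

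- **If individual:** replace the t test and Mann-Whitney U with a pre-specified paired analysis, or a mixed model with case status as a fixed effect and pair as a random effect. The mixed model keeps women whose partner has missing data. Check distributions on within-pair differences or residuals, and use Wilcoxon signed-rank as a sensitivity check.
- **If by frequency:** regress each outcome on case status, adjusted for the matching factors.

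In either case, fix the effect measure for each outcome in advance instead of letting a Shapiro-Wilk pre-test choose it, and keep RHI on its measured scale so that the analysis estimates the 0.3 difference used for sizing.

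The change is to analysis wording and needs no new data, beyond keeping the pair identifier if matching is individual. If rho turns out to be 0, it costs about 1 power point (79.5% paired against 80.4% unpaired at 45 per group). One practical limit is that the article subdivides placental nitric oxide samples by labour, which is not a matching factor, so some pairs may differ on it. A simple paired test within labour strata would lose those pairs; a mixed model with labour as a covariate would keep them.

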### Objectives

#### Primary study objective

To evaluate OS during pregnancy.

Measurement of •NO in placental tissue and O_2_•^−^ in maternal blood using EPR.

Measurement of eNOS in placental tissue using immuno-histochemical staining.

*Prospective longitudinal study*: To evaluate the OS profile in normal pregnancies.

*Matched case-control study:* To compare the OS profile in normal versus PE pregnancies.

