##### Exclusion criteria

Exclusion criteria are (gestational) diabetes, multiple pregnancies, fetal abnormalities, hypercholesterolemia, renal disease, auto-immune disorders and connective tissue disease. Intake of low-dose aspirin or vitamin C supplements (> 500 mg/day) is an exclusion criterion. Since in Belgium folic acid is an advised pre- and periconceptional therapy, this will not act as an exclusion criterion.

The use of other medication/supplements will be listed in the patients record to find eventual confounders afterwards.

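### In the case-control study a normality test on the data chooses the analysis of each marker, and its rank-test branch names no effect estimate or interval, even for the primary oxidative stress markers

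*Protocol article*

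**What the plan says.** The primary objective is "To evaluate OS during pregnancy", measured by •NO and eNOS in placental tissue and O2•− in maternal blood. For the case-control arm it becomes "To compare the OS profile in normal versus PE pregnancies" (Protocol article, Primary study objective).

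The analysis rule is in Descriptive statistics and data analysis, Matched case-control study. Twelve named items, with eNOS, •NO and O2•− among them, and all other continuous variables "will be tested for normality using the Shapiro Wilk Test". Where normality holds, "they will be expressed as mean, standard deviations and 95% confidence intervals and compared using two sided T test". Where it does not: "If not, they will be expressed as median and interquartile ranges and compared using Mann Whitney U Test".

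Four other places bear on the point:
- Sample size calculations says of RHI, the variable used for sizing, that "there is normal distribution and the population standard deviation is known". No distribution, SD or CV is given for •NO, O2•− or eNOS.
- Placental concentration of •NO states that labour affects placental NO and splits the samples into labour and no labour.
- Exclusion criteria has other medication and supplements recorded "to find eventual confounders afterwards".
- Multicentre matched case-control study matches on six factors: maternal age, gestational age, parity, smoking, BMI and ethnic group.

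**The concern.** The t test compares means and the Mann-Whitney test compares ranks. Under this rule the same marker could be reported either way, depending on whether one test of shape in 45 women per group crosses its threshold. The rule is also incomplete. It gives no significance level for the Shapiro-Wilk test, and it does not say whether each group or the pooled sample is tested, or what follows if only one group fails. Two analysts could take different branches from the same data.

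The rank branch promises two medians, two interquartile ranges and a p-value. For a study whose primary aim is to compare oxidative stress between pre-eclamptic and normal pregnancies, the size of the difference and its uncertainty are the main results, and that branch names neither.

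A separate weakness lies beside this. Neither two-group test has room for a covariate, while the article itself identifies labour as an influence on one primary marker.

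**Working it through.** **The plan's own figure.** The inputs are in Sample size calculations, Matched case-control study: "the RHI in normotensive pregnancies was 1.8, and in PE 1.5", SD 0.5, relevant difference 0.3, 80% power, two-sided 0.05. By the normal approximation, n per group = 2 × (1.960 + 0.842)² × (0.5/0.3)² = 2 × 7.85 × 2.78 ≈ 43.6, so 44. This reproduces the stated 44. The t distribution gives 44.6, so 45, which is the planned number. The effect size is 0.3/0.5 = 0.6 SD.

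**If the data are perfectly normal.** With each group tested at 0.05, a marker fails in at least one group with probability 1 − 0.95² = 0.0975, about 10%. For the three primary markers, taken as independent, at least one is sent to the rank branch with probability 1 − 0.95⁶ = 0.26. For all twelve listed items it is 1 − 0.95²⁴ = 0.71. So the choice of analysis is partly noise without any assumption of skewness.

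**If the markers are right-skewed.** Assumptions, none of them given by the article: lognormal data with σ = √ln(1 + CV²), Shapiro-Wilk at 0.05 in each group of 45, and a switch to Mann-Whitney if either group fails. Results are from 3,000 simulated studies per row. The power columns use a true shift of 0.6 SD on the log scale (0.6 SD for the normal row).

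| CV | One given group fails | Either group fails | Type I error, planned rule | Power, planned rule | Power, log-scale t test |
|---|---|---|---|---|---|
| normal data | 0.051 | 0.102 | 0.051 | 0.808 | 0.811 (no log taken) |
| 10% | 0.110 | 0.203 | 0.051 | 0.801 | 0.801 |
| 20% | 0.271 | 0.472 | 0.053 | 0.781 | 0.788 |
| 30% | 0.522 | 0.772 | 0.053 | 0.798 | 0.803 |
| 40% | 0.719 | 0.925 | 0.051 | 0.802 | 0.817 |
| 50% | 0.870 | 0.982 | 0.050 | 0.790 | 0.802 |
| 100% | 0.999 | 1.000 | 0.054 | 0.785 | 0.803 |

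The either-group column agrees with 1 − (1 − p)²; at CV 30%, for example, 1 − 0.478² = 0.772. A second simulation gave 19%, 46%, 77%, 92% and 98% at CVs of 10% to 50%. The simulation standard error is at most √(0.25/3000) ≈ 0.009, so the two runs agree.

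**Reading the table.** The first two columns show that the route taken depends strongly on a CV that the article does not state. The last three show that the planned rule holds its error rate and loses almost no power. Any damage is therefore to what is estimated and reported.

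**The two branches side by side.** The t-test branch lists a 95% CI, but among the descriptive summaries, so it is not clearly an interval for the difference. The rank branch lists no interval at all. Neither names a transformation, a covariate or an analysis that uses the matching.

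**The case against.** The strongest reply is that the procedure does no inferential harm. Type I error stays near 0.05 and power near its target. An effect measure to go with a rank test is also a detail that a condensed article may leave to a fuller document. The first part stands and limits the point to estimation and interpretation. The second stands only in part: the article does not leave the choice open but fixes a rule for it, and the rule lets the data choose the quantity reported.

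A reader might infer three stronger claims that the document does not support:

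- *That the primary markers will most likely end in the rank branch.* The article gives no distribution or CV for them. At a CV of 10%, or with normal data, most studies would stay with the t test. At 20% it is roughly even if either group triggers the switch, and 27% if a single group decides.
- *That the normality test prevents adjustment for confounders.* The t-test branch has no covariates either, so removing the normality test would not by itself add adjustment. There is also partial control already: matching on six factors and the split by labour. Nothing forbids a later analysis of the recorded medication.
- *That testing RHI for normality contradicts the sample size section.* Assuming normality for sizing and then checking it in the data is not a contradiction.

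It is also fair that two medians with interquartile ranges show the direction and rough size of a difference. What they lack is an estimate of the contrast with its uncertainty.

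**Conclusion.** The point holds as a should-fix matter of estimation and interpretability. For •NO, O2•− and eNOS the reported quantity is chosen by a significance test of the sample's shape, under a rule with no stated level or unit of testing, and one of its two outcomes names no effect estimate or confidence interval. That outcome is reached in about 10% of studies per marker with normal data. With lognormal data it is about 19–20% at a CV of 10%, 47% at 20%, 77% at 30% and 92% or more from 40%. All of these assume 45 per group, a level of 0.05 and the either-group trigger. The probabilities are conditional on those assumptions and are not a forecast for this study. There is no case that the false-positive rate or the power is at risk.

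The missing covariate is a second, separate weakness. It applies to both branches and matters most for placental •NO, where the article names labour as an influence but handles it only by subdividing. That splits the 45 per group and gives no single adjusted comparison.

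**What to change.** Remove the Shapiro-Wilk test as the rule that selects the analysis, and fix one analysis per primary marker before the data are seen:

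- **•NO and O2•−:** a linear model on the log scale, reporting the ratio of geometric means with a 95% CI.
- **eNOS:** a scale fixed in advance to suit the staining score, or Mann-Whitney with a Hodges-Lehmann shift and 95% CI.
- **RHI** (the sizing variable): the original scale, with a mean difference and 95% CI.

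Include labour status as a covariate for placental •NO, and account for the six matching factors in the models. Check the models with residual plots, and keep the rank test as a sensitivity analysis.

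The cost is in the analysis text only. No sample size, visit or measurement changes, and in the simulation the log-scale analysis had power of 0.79–0.82 against 0.78–0.81 for the planned rule. Log-scale results need a sentence of explanation, and the analysis section becomes slightly longer.

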## Discussion

PE is responsible for 11.5% of maternal deaths in Flanders. Ten percent of early neonatal deaths are caused by maternal hypertensive disorders [39]. This project will contribute to the knowledge of PE with the ultimate goal of reducing maternal morbidity and mortality.

As stated before, the gold standard for non-invasive assessment of endothelial function is FMD [26]. Previous literature suggests that during normal pregnancy, there is a steady increase in FMD until week 32, with a stabilization or even decline at week 36 [40]. In PE, a significant reduction in FMD is suggested [41]. Data using PAT during pregnancy and PE are limited, based on small studies and they show opposing results [38, 42]. Due to measurement of peripheral microcirculatory function, PAT is less NO-dependent than FMD. As such, FMD and PAT assess different aspects of vascular function [43–45]. Arterial stiffness has been evaluated in pregnancy, using applanation tonometry (AP) [2]. During normal pregnancy AIx falls during mid pregnancy and rises at the end of pregnancy. In PE AIx is significantly increased and a significant role of first trimester AIx in the early screening of PE has been proposed [2]. Arterial stiffness is independently associated with cardiovascular risk and may, therefore, provide a potential marker to select women who will develop cardiovascular events later in life after PE [2, 46]. Concerning endothelial function and arterial stiffness in normal pregnancy and PE there is still no consent in literature and further research is warranted.

Both in normal pregnancy and PE are inflammatory effects present, which can be objectified by higher neutrophil to lymphocyte ratio (NLR) and higher mean platelet volume (MPV) [47]. Increase in NLR and MPV are described to be more prominent in PE, and these factors have been proposed as predictive biomarkers for PE [31, 48]. Increased systemic low grade inflammation possibly contributes to alterations in endothelial function.

Previous research has demonstrated that markers of OS, like O_2_•^−^, hydrogen peroxide (H_2_O_2_), hydroxyl radical (•OH), nitric oxide (•NO), and peroxynitrite (ONOO^−^) are involved in the pathophysiology of placental pregnancy disorders. OS at the site of the placenta causes placental damage and this ischemic placenta releases cytotoxic, anti-angiogenic and inflammatory markers in the circulation resulting in systemic endothelial dysfunction and peripheral organ damage [3]. O_2_•^−^, the most abundant free radical, encloses an important role in the beneficial effects of OS. Studies measuring O_2_•^−^ concentration longitudinally in normal pregnancy and during PE are lacking, creating a gap in the knowledge of OS in pregnancy and PE. Evidence for OS at the placenta and in the maternal circulation in PE has led to the suggestion that anti-oxidant therapy can improve or even prevent PE. Vitamins E and C, L-arginine (precursor of •NO) and •NO donors have been proposed to limit both endothelial injury and for the prevention of PE with conflicting results [49–55]. Substantial knowledge of the evolution of OS in healthy and PE pregnancies might influence introduction of these therapies in regular medical practice.

ENDOPREG is the first clinical study comparing in vivo measurements of endothelial function with in vitro markers of endothelial dysfunction in a longitudinal and case-control setting. To our knowledge, serial changes in maternal endothelial function have not been evaluated previously in pregnancy using two different methods, i.e. PAT/FMD and EPR, simultaneously. The main strength of our study is the longitudinal design. Little studies determined maternal •NO or reactive oxygen species concentration at the moment of diagnosis [56] and only a few performed a longitudinal approach. Studying endothelial function and OS profile in and after normal pregnancies and PE, will give a better insight in the pathophysiology of this pregnancy complication and will help with the detection of patients a risk of developing cardiovascular events later in life. Within the ENDOPREG study, research groups from biomedical and pharmaceutical sciences will collaborate to unravel yet another step in the pathophysiology of the disease of many theories, PE.

